### Secondary outcomes

#### Quit rates

Although not adequately powered for detecting small differences in the secondary outcomes, Fisher’s exact test will be used to detect potential differences in smoking cessation rates between groups and to demonstrate potential effectiveness of the intervention. Differences between experimental groups in the secondary outcome - PHQ2 will be assessed using the Kruskal-Wallis test. Fisher’s exact tests will be used to compare conditions on post-partum smoking rates at 6 weeks after delivery.

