### Secondary outcome measures

To measure participants’ self-reported smoking status women will complete one baseline and eight follow-up self-report touchscreen computer surveys. The computer survey was programed using Digivey survey software
[23]. Use of computer surveys to assess smoking status has been shown to be a reliable and accurate method of data collection
[24], as well as being reported as enjoyable and easy to complete by most participants
[22].Questions assessing participants’ demographic characteristics and factors previously found to be associated with smoking status will also be included. The following questions will be included in the self-report, touchscreen computer surveys:

*Baseline survey*:

• *Smoking status and history* will be assessed through standardised questions or questions adapted from previous research
[22,25-32] with many items based on the previous the work of Bryant et al.
[22,26,27] Items will include: current smoking status
[22,26], number of cigarettes currently smoked per day
[30], smoking history, previous quit attempts, reductions in smoking
[25,26], strategies used to assist in previous quit attempts
[26,27], readiness/stages of change
[29,31], financial stress
[33,34], whether they smoked during any previous pregnancies
[32]and whether they attempted to quit or reduced smoking during any previous pregnancies
[26,32]. Questions assessing women’s exposure to environmental smoke will also be included
[25,26,32].

• *Demographic characteristics*: women will be asked to answer questions relating to their: age, date of birth, highest level of education, Aboriginal or Torres Strait Islander status, current household income, marital status, number of previous pregnancies, gestation period, postcode, number of adults and children (<18 years) residing in their household.

• *The Patient Health Questionnaire**2* (*PHQ2*)
[35]: Will be included as a short, simple measure of participants’ levels of depression. The PHQ2 consists of two questions, which assess respondent’s level of depressed mood in the previous 2 weeks
[35]. Respondents rate the frequency of depressed mood and anhedonia on a four point likert scale, ranging from 0 (“not at all”) to 3 (“nearly every day”)
[35]. Total score on the PHQ2 range from 0 to 6. A score of 4 has recommended as an appropriate cut-point for screening for possible depressed mood in pregnant women

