[36]. The PHQ-2 has evidence of criterion validity; as well as acceptable specificity (92%) and sensitivity (83%)
[35]. Previous research has found a relationship between depression and smoking status
[37,38].

• *Economic questions*: Women will be asked to a number of questions relating to their personal out-of-pocket costs, time costs and health care utilisation incurred as a result of the intervention.

• *Social characteristics*: women will be asked whether their partner or others within their household smoke.

*Follow*-*up surveys*: During each of the follow-up visits, women will be asked to complete a brief touchscreen computer survey using a number of items from the baseline survey. Questions will assess their current smoking status, number of cigarettes smoked per day (if they have not abstained), changes in smoking behaviour, partners’ current smoking status, exposure to environmental smoke, the number of quit attempts made, gestation age; the PHQ2 and efforts to engage with quit smoking support services.

The following two biochemical analyses will be used to validate women’s self-reported smoking status:

1. *Saliva cotinine analysis*: will be used to biochemically validate self-reported smoking status for all participants at baseline and each of the eight intervention sessions using the NicAlert® semiquantitative dipstick assay. A previous study analysing 167 family practice patients using NicAlert® illustrated acceptable levels of sensitivity (99%) and specificity (96%)
[11].Cotinine analysis with the NicAlert® dipstick takes approximately 20 minutes and can be performed by untrained persons, highlighting the potential utility of such a test in clinical practice .

2. *Hair cotinine analysis*: will be undertaken during the eighth or final intervention session. Participants will be asked to provide a small sample of hair taken from the nape of the neck. Samples will be transported to an off-site laboratory for analysis. Hair cotinine analysis can reliably quantify long-term exposure to tobacco, with each centimetre of scalp hair representing approximately 1 month of past exposure
[39]. Gas chromatography – mass spectrometry will be used to analyse hair cotinine levels, as it is considered the standard reference in analysis of cotinine
[40]. A cut-point of 0.2 ng/mg has been found to distinguish between pregnant active smokers and passive or unexposed with high levels of sensitivity (91%), specificity (94%) and test accuracy (91.7%)

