### Analysis

Baseline demographic and social characteristics of patients in all the three treatment groups will be summarised separately. Continuous data will be expressed as mean values with standard deviations (SD), and categorical data will be presented as counts with percentages.

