### Primary outcomes

Proportions and frequencies will be calculated to assess the following outcomes: (i) participant consent rates; (ii) loss to follow-up rates; and (iii) participant compliance with saliva and hair cotinine analysis. Proportions and frequencies will also be calculated for all closed-ended questions included in the study participant and clinic staff interviews to allow investigation of: (iv) participant acceptability of touchscreen computers for self-reported smoking rates and demographics; and (v) acceptability of incentives to staff and study participants. Differences between experimental groups in the proportion of each of these five primary outcomes and the secondary outcome (proportion quit smoking) will be assessed through Fisher’s exact test. Differences between participant subgroups and these outcomes will also be assessed using Fisher’s exact test. Although p-values from the above will be reported, the focus will be on providing 95% confidence intervals around point estimates for comparisons of all three treatment arms.

Qualitative analysis will be performed on open-ended questions included in participant and staff interviews investigating the following primary outcomes: (vi) acceptability of saliva and hair cotinine analyses for biochemical validation of smoking status; and (vii) perceived barriers and facilitators to using financial incentives. All interviews will be transcribed verbatim and a thematic analysis will be performed independently by two of the research team members.

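### The planned Kruskal-Wallis test of PHQ-2 makes no use of the baseline PHQ-2 already collected; adjusting for it is a minor improvement at no cost

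*Protocol article*

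**What the plan says.** All references are to the Protocol article.

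- **Collection.** Under Secondary outcome measures, "women will complete one baseline and eight follow-up self-report touchscreen computer surveys". PHQ-2 is a baseline item, described as a "short, simple measure of participants’ levels of depression". The follow-up survey items include "gestation age; the PHQ2 and efforts to engage with quit smoking support services". Each woman should therefore have a baseline score and up to eight follow-up scores.
- **Scale.** "Total score on the PHQ2 range from 0 to 6", so the outcome is ordinal with seven levels.
- **Test.** Under Quit rates, PHQ-2 is called a secondary outcome, and differences between the experimental groups in "PHQ2 will be assessed using the Kruskal-Wallis test". No covariate, change score or visit is named.
- **Use of baseline data.** Under Analysis, "Baseline demographic and social characteristics of patients in all the three treatment groups will be summarised separately". This is description only. Nothing else in the document says how baseline PHQ-2 would be used.

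**The concern.** The baseline value of the same instrument is usually among the better predictors of its follow-up value. A comparison that leaves it out treats predictable differences between women as noise. It also passes part of any chance difference between arms at baseline into the follow-up comparison. With 30 women per arm precision is scarce, and the protocol itself says that it is not powered for small differences in secondary outcomes.

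The protocol names the test, so this is a stated choice and not a detail left open for an analysis plan. What is at stake is the precision and readability of the PHQ-2 comparison. The feasibility results and the quit-rate comparison are unaffected.

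**Working it through.** **Inputs from the document.** Three arms of 30 women; 20% drop-out allowed for (Sample size), so about 30 × 0.8 = 24 analysed per arm; PHQ-2 scored 0 to 6. No power, variance or target difference is given for PHQ-2, so there is no figure to reproduce. The stated 68% power concerns smoking rates and has no bearing here.

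**Assumed input.** The correlation ρ between baseline and follow-up PHQ-2 is not given. The range 0.3 to 0.7 is used.

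**Step 1: variance.** For a linear baseline-adjusted comparison, adjusted variance ÷ unadjusted variance = 1 − ρ². The equivalent unadjusted arm size is 30 ÷ (1 − ρ²). A change score has variance 2(1 − ρ) relative to the unadjusted score.

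| ρ | 1 − ρ² | 30 women do the work of | change score, 2(1 − ρ) |
|---|---|---|---|
| 0.3 | 0.91 | 33 | 1.4 |
| 0.5 | 0.75 | 40 | 1.0 |
| 0.7 | 0.51 | 59 | 0.6 |

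For a seven-level score analysed by ranks these are approximations, so the tests themselves were simulated in Step 3.

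**Step 2: chance imbalance.** The standard error of the baseline difference between two arms is √(2/30) = 0.26 SD, or √(2/24) = 0.29 SD with 24 per arm. An unadjusted follow-up comparison carries ρ times the baseline gap. For a gap of one standard error at n = 30 this is 0.3 × 0.26 = 0.08 SD to 0.7 × 0.26 = 0.18 SD.

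**Step 3: simulation on a 0–6 score.** Latent normal baseline and follow-up scores were cut into seven levels with assumed probabilities 0.30, 0.20, 0.20, 0.12, 0.10, 0.05 and 0.03. The arm shifts were 0, 0.4 and 0.8 latent SD, with women drawn independently and 2,000 trials per setting. The Monte Carlo standard error is about √(0.7 × 0.3 / 2000) = 1 percentage point.

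| latent ρ | n per arm | Kruskal-Wallis power | rank ANCOVA power |
|---|---|---|---|
| 0.3 | 30 | 70% | 73% |
| 0.5 | 30 | 70% | 79% |
| 0.7 | 30 | 70% | 89% |
| 0.3 | 24 | 57% | 60% |
| 0.5 | 24 | 56% | 65% |
| 0.7 | 24 | 58% | 79% |

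With no true effect, Kruskal-Wallis rejected in 4.0% to 6.1% of trials and rank ANCOVA in 3.9% to 5.9%. Both hold their level.

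**Step 4: small effects.** With shifts of 0, 0.1 and 0.2 SD, power is about 9% for Kruskal-Wallis and 10% to 12% for the adjusted test. If the effect on mood is small, neither test is likely to detect it.

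**Step 5: an imposed imbalance.** Suppose there is no true effect but one arm is 0.5 SD away from the other two at baseline. At a correlation near 0.5, Kruskal-Wallis then rejects in roughly 14% to 17% of trials; near 0.3 the figure is 7.5% to 9%. The adjusted test stays at about 5%. Such a gap is uncommon: for one pre-chosen arm against the other two it is 0.5 ÷ √(1/30 + 1/60) = 2.2 standard errors. Under individual randomisation, some arm lies that far out in about 6% to 7% of trials.

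**The case against.** The strongest reply is that the planned test is valid, that PHQ-2 is peripheral, and that the benefit rests on figures the document does not supply. Most of this stands. PHQ-2 appears in none of the listed primary or secondary aims; only the Quit rates section calls it an outcome. The document gives no correlation and no expected effect on mood. The power gains in Step 3 assume large shifts, and Step 4 shows that with small shifts they almost vanish. Only rank ANCOVA was simulated, not the proportional-odds model.

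A second reply is that the test might be run on change from baseline, which would use the baseline score. The text does not say so. Even then, the table in Step 1 shows that a change score has higher variance than the adjusted analysis at every assumed correlation, and higher variance than no adjustment when ρ is below 0.5.

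A reader might also draw three stronger conclusions that the document does not support:

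- **Conflict with the emphasis on intervals.** Under Primary outcomes the protocol says "the focus will be on providing 95% confidence intervals around point estimates". That sentence refers back to the Fisher comparisons of the primary outcomes and the proportion who quit. PHQ-2 enters the analysis only later, under another heading, so there is no contradiction.
- **Inflated type I error.** The 17% is a rejection rate conditional on an imposed 0.5 SD imbalance at moderate correlation. Averaged over randomisation, the error rate is near 5%.
- **A remedy for allocation by clinic session.** Randomising by day and session may make baseline differences more plausible, but adjusting for baseline PHQ-2 does not deal with that allocation or any clustering from it. The simulations drew women independently.

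**Conclusion.** The point holds as a minor one. The planned comparison of PHQ-2 is valid on average but makes no described use of a baseline score that is already collected. It therefore loses precision and leaves chance baseline differences in the result. At assumed correlations of 0.3, 0.5 and 0.7 the adjusted variance would be about 0.91, 0.75 and 0.51 of the unadjusted value. That range runs from a small gain to a substantial one, and the document does not show where in it the trial lies.

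The conclusion that adjustment helps needs only a non-trivial correlation between baseline and follow-up. The power figures need more: the assumed score distribution, the assumed shifts, and independent women. They are illustrations, not forecasts. No primary conclusion of this feasibility pilot depends on the point.

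**What to change.** In the Quit rates section, replace the PHQ-2 sentence with a baseline-adjusted analysis:

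- Name one follow-up session in advance as the time point for PHQ-2.
- Compare the arms at that session with baseline PHQ-2 as covariate, either by rank ANCOVA or by a proportional-odds model reporting the adjusted odds ratio with 95% CI for each arm comparison.
- Keep the Kruskal-Wallis test as a sensitivity analysis.

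The cost is a sentence or two of analysis wording, with no extra data, visits or participants. The proportional-odds model adds the proportional-odds assumption, which should be checked; rank ANCOVA avoids it but gives no odds ratio. The new wording should not be presented as dealing with allocation by clinic session.

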#### Validation analysis of saliva and hair cotinine compared to self-report smoking rates

Agreement between self-reported smoking status and the cotinine saliva test strip will be assessed using the Kappa statistic. Agreement between self reported smoking status and hair cotinine results will also be assessed using the Kappa statistic.

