### Aims

The primary aim of this study is to test the feasibility of a personal financial incentive (PFI)-based intervention at encouraging smoking cessation in pregnant women attending an Australian public hospital for antenatal care. Specifically, the study will assess: (i) consent rates of women to participate in the trial; (ii) loss to follow-up rates of study participants; (iii) compliance with saliva cotinine and hair cotinine analyses for biochemical validation (iv) acceptability of using a touchscreen computer for self-reported smoking status and demographics; (v) acceptability of saliva cotinine and hair cotinine analyses for biochemical validation of smoking status; (vi) acceptability of incentives of varying magnitude ($20 vs. $40) to staff and study participants; and (vii) the perceived barriers and facilitators to using financial incentives in a public antenatal clinic among clinic staff. Additionally, secondary aims include: (i) to assess the potential effectiveness of the varying PFI amounts ($20 vs. $40) in reducing smoking among study participants; (ii) to assess the accuracy of self-report smoking status with saliva and hair cotinine analysis; and (iii) to undertake a cost-effectiveness analysis comparing the changes in costs of the intervention and changes in quit rates between each arm of the trial.

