### Participants

A sample of ninety (90) consenting pregnant women will be recruited to participate. Women will be considered eligible if they are: (1) aged at least 16 years; (2) presenting for their first antenatal visit; (3) less than 31 weeks gestation; (4) sufficient in English language to complete the survey; and (5) a current smoker (defined as having smoked in last 7 days and a return a positive saliva sample for cotinine). Pregnant women will be ineligible to participate if they have elected to receive shared antenatal care with their GP and/or are considered by clinic staff to have a severe cognitive or psychiatric disorder; currently being treated for chemical dependency other than alcohol or tobacco; or have quit smoking before their first antenatal appointment.

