### Procedures

All women who visit the hospital antennal clinic will undergo their usual antenatal interview by the clinic nurse. During this interview patients are asked about their smoking status and basic demographic characteristics. At this time potentially eligible patients will be identified and informed that the study is being conducted within the clinic. If women are interested they will be directed to a Research Assistant (RA) who will be stationed within the clinic. The RA will provide interested women with information describing the study. If patients would like to take part in the study the RA will obtain their written informed consent. Women will then be asked to provide a saliva sample to confirm their smoking status and complete a 15-minute baseline Touchscreen computer survey, which will also ask for their on-screen consent.

If a woman’s initial antenatal appointment has been randomised to one of the two intervention groups, the RA will verbally explain the details of their incentive scheme, including, the schedule for monitoring, contingencies being offered and the rules of payment. All participants will be provided with a study package to take home with them, which will contain information about the study, referrals to Quit smoking self-help documents and a Quit telephone help number (provided by clinic midwives) and a letter of support to pass onto their partner. Consenting women will be asked to attend 8 intervention sessions, at which participants in the two intervention groups will be eligible to receive a reward. The 8 intervention sessions will occur approximately fortnightly, during participants’ scheduled antenatal appointments.

During each of the 8 intervention sessions, all women will be asked to indicate their current smoking status and whether they have quit smoking in the last 7 days. Women will also be asked to provide a saliva sample which will be analysed to confirm their self-report smoking abstinence. Those women in the intervention groups who self-report non-smoking and return a negative cotinine reading (level 0) will be provided with their monetary incentive. A similar follow-up procedure will occur seven more times (i.e. a total of 8 intervention sessions) during women’s scheduled antenatal appointment.

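### Accuracy of self-report is to be judged by kappa alone, and for hair no rule matches the self-report period to the months of hair tested

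*Protocol article*

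**What the plan says.** The Aims section gives secondary aim (ii) as "to assess the accuracy of self-report smoking status with saliva and hair cotinine analysis". The validation analysis section answers it with two statistics. For saliva, "Agreement between self-reported smoking status and the cotinine saliva test strip will be assessed using the Kappa statistic". For hair, "Agreement between self reported smoking status and hair cotinine results will also be assessed using the Kappa statistic". It names no other measure and does not say which sessions, which self-report item or which period enter either kappa.

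The measurements are described elsewhere in the article:

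- **Self-report.** Under Procedures, at each of the eight sessions "all women will be asked to indicate their current smoking status and whether they have quit smoking in the last 7 days". Sessions are about two weeks apart.
- **Saliva.** Under Secondary outcome measures, it is taken "at baseline and each of the eight intervention sessions".
- **Hair.** It is taken once, at the eighth or final session, to assess long-term smoking, with "each centimetre of scalp hair representing approximately 1 month of past exposure". The length is not given: "Participants will be asked to provide a small sample of hair taken from the nape of the neck". The same section says that hair will in turn be validated against self-report and saliva over the course of the study.
- **Entry.** Under Participants, a current smoker is defined as "having smoked in last 7 days and a return a positive saliva sample for cotinine".

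**The concern.** There are two separate difficulties.

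First, the aim is accuracy, which has a direction: cotinine is the reference and self-report is being judged. Kappa is symmetric, so exchanging the two kinds of disagreement leaves it unchanged. It cannot show how often a claim of abstinence is false. That is the error of most interest in a trial that pays two of its three arms for abstinence, and it might differ between paid and unpaid women.

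Second, hair and self-report describe different periods. Every participant was a verified smoker at entry. A woman who stopped part-way through and says so truthfully at the last session can still have cotinine in hair grown before she stopped. Without an alignment rule she is scored as a disagreement. A low hair kappa could then be taken as false reporting or, since the plan also uses the comparison to validate hair, as poor performance of the hair test. Neither need be true.

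**Working it through.** The plan states no expected kappa or precision for this analysis, so there is no figure of its own to reproduce. Throughout, kappa = (po − pe)/(1 − pe), where po is observed and pe chance-expected agreement.

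**Inputs from the protocol article.** 90 women and 20% drop-out (Sample size); hair sensitivity 91% and specificity 94%, saliva 99% and 96% (Secondary outcome measures); self-report underestimating smoking by as much as 25% (Background).

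**Assumed inputs.** The share q of women abstinent at the last session is 10% to 30%. The share r of truthful quitters whose hair segment still covers smoking is 0 to 1. The 25% is applied as a quarter of current smokers denying smoking.

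**1. Time covered.** 8 sessions × 2 weeks = 16 weeks from entry to the hair sample, about 3.7 months or 3.7 cm. A longer segment reaches back to entry, when all participants smoked.

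**2. Hair, all women truthful, perfect test.** 90 × 0.8 = 72 samples; assume 18 abstinent (q = 25%).
- 9 of 18 recent quitters: the cells are 54 smoker/hair-positive, 0 smoker/hair-negative, 9 abstinent/hair-positive, 9 abstinent/hair-negative. po = 63/72 = 0.875. pe = 0.75 × 0.875 + 0.25 × 0.125 = 0.6875. Kappa = 0.1875/0.3125 = 0.60.
- 12 of 18 recent: po = 60/72 = 0.833. pe = 0.75 × 0.917 + 0.25 × 0.083 = 0.708. Kappa = 0.125/0.292 = 0.43.

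With aligned windows and the same perfect test, kappa would be 1.

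**3. Range over q and r, all women truthful.**

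| r | Perfect test, q = 10 / 20 / 30% | Stated hair accuracy, q = 10 / 20 / 30% |
|---|---|---|
| 0 | 1 / 1 / 1 | 0.64 / 0.76 / 0.82 |
| 0.5 | 0.64 / 0.62 / 0.58 | 0.37 / 0.45 / 0.46 |
| 0.75 | 0.38 / 0.35 / 0.32 | 0.20 / 0.24 / 0.25 |
| 1 | 0 / 0 / 0 | 0 / 0 / 0 |

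**4. Can hair kappa separate timing from false reports?** Take q = 20% and the stated hair accuracy.
- No false reports, r = 0.5: quitters are hair-positive with probability 0.5 × 0.91 + 0.5 × 0.06 = 0.485. po = 0.8 × 0.91 + 0.2 × 0.515 = 0.831. pe = 0.8 × 0.825 + 0.2 × 0.175 = 0.695. Kappa = 0.136/0.305 = 0.45.
- 25% of smokers deny, windows aligned (r = 0): the cells are 0.546 (both positive), 0.054 (self-report positive only), 0.194 (hair positive only), 0.206 (both negative). po = 0.752. pe = 0.6 × 0.74 + 0.4 × 0.26 = 0.548. Kappa = 0.204/0.452 = 0.45.

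The two situations give the same kappa.

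**5. Follow-up saliva against self-report.** With truthful women, kappa is 0.929, 0.950 and 0.955 at q = 10%, 20% and 30%. With 25% of smokers denying, it is 0.355, 0.518 and 0.611. This comparison does respond to misreporting.

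**6. What kappa leaves out.** At q = 20% with 25% denial, the saliva cells are 0.594 (both positive), 0.006 (self-report positive only), 0.206 (saliva positive only) and 0.194 (both negative). Kappa is (0.788 − 0.56)/0.44 = 0.518. The cotinine-positive share of claimed abstinence is 0.206/0.400 = 51.5%, the sensitivity of self-report is 0.594/0.800 = 74%, and its specificity is 0.194/0.200 = 97%. Swap the two discordant cells, purely as an arithmetic illustration, and kappa is still 0.518, but the false share of claimed abstinence is 0.006/0.200 = 3%.

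**7. Baseline.** Among enrolled women, self-report and saliva are both positive by eligibility, so po = pe = 1 and a baseline-only kappa is 0/0. Pooling one baseline pair with eight follow-up pairs per woman moves the 25%-denial values from 0.355 to 0.368, from 0.518 to 0.537 and from 0.611 to 0.634.

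**The case against.** Kappa is a standard agreement measure, and the 2×2 table behind it also yields sensitivity, specificity and the false-abstinence proportion, which the article does not rule out reporting. Hair length and the derivation of a matched self-report variable commonly sit in a laboratory manual or analysis plan, and the absence of such detail from a journal article is not in itself a fault. Comparing hair with the other measures over the whole study could mean a cumulative self-report status. The aim is secondary in a pilot, rewards depend on self-report plus a negative saliva test, and no primary feasibility outcome uses the hair kappa.

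Much of this stands, and it rules out three stronger readings that a reader might infer:

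- **That self-report accuracy goes unmeasured.** It does not. Saliva and 7-day self-report are collected together at eight follow-up sessions, are matched in time and are not forced to agree by eligibility (step 5).
- **That the plan compares hair with the last 7-day answer.** The article does not say so. What can be said is that the self-report to be compared with hair is left open, and one natural choice gives a misleading result.
- **That baseline pairs seriously inflate the saliva kappa.** The article does not say that they enter it, and including them changes kappa by only about 0.01 to 0.02 (step 7).

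What the objection does not remove is that the article does choose a statistic for an accuracy aim, and the one it chooses cannot express accuracy. Nor does a comparison over the whole study settle alignment without a rule for combining sessions.

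**Conclusion.** The point holds as a moderate weakness in the analysis of one secondary aim. Kappa alone does not answer a question about accuracy: on the figures in step 6, the same value of 0.518 goes with a false share of claimed abstinence of either 51.5% or 3%. For hair, the period is not aligned with self-report, so timing alone can lower kappa. On the assumed 72 samples with 18 abstinent, 9 to 12 recent quitters, perfect tests and no misreporting, it falls from 1 to between 0.60 and 0.43. With the stated hair accuracy, aligned truthful reports would give only 0.64 to 0.82, and 0.37 to 0.46 if half of the quitters are recent.

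These sizes rest on the quit share and the share of recent quitters, which the article does not give. Depending on those and on segment length, the effect runs from none to total. The conclusion that hair kappa cannot by itself tell false reports from honest recent quitting does not depend on one particular value.

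**What to change.** 1. **Saliva.** Use follow-up sessions only, with confidence intervals clustered on woman because each contributes up to eight pairs. Lead with the proportion of self-reported abstinence that is cotinine-positive, then sensitivity and specificity of self-report against cotinine. Report these overall and by arm, with kappa as a supplement. The by-arm figures should be descriptive: 18 abstinent women over three arms would be about 6 per arm.
2. **Hair.** State the segment length before assay, since a sample assayed whole cannot be divided afterwards. Compare the result with all sessions within the months that the segment covers, counting a woman as a smoker if any session in that window is positive by self-report, and separately by saliva. This keeps the long-term purpose for which hair is collected, which restricting the assay to the most recent centimetre would give up. Two limits should be noted in the plan. Fortnightly 7-day reports cover about half of the days (7 of 14), so some mismatch remains. A segment reaching back to entry makes every woman a smoker by eligibility and leaves nothing to compare.

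The cost is a little more analysis work and a laboratory record of hair length. No extra women, samples or assays are needed.
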